**Overview**

The present study is a randomised control trial investigating the effects of a short six week exercise training program in colorectal cancer patients following neoadjuvant chemoradiotherapy prior to elective colorectal cancer surgery. All patients will attend 5 sets of appointments at the hospital for diagnostic tests and **3 appointments at the University of Liverpool Magnetic Resonance and Image Analysis Research Centre (MARIARC)** (listed below). **Three** appointments will be prior to chemoradiotherapy treatment, and the other **4** will be after chemoradiotherapy. Two of these 5 appointments are part of routine care. The first **4** appointments will last about an hour. Patients will complete 3 quality of life questionnaires on recruitment, during chemotherapy, before and 4-6 weeks after surgery. These 3 questionnaires will take 20 minutes to fill in. The fourth and fifth appointments will consist of Computed Tomogram (CT) and Magnetic Resonance Imaging (MRI) scans in our radiology department to assess cancer staging. These appointments will last about 1 hour 30 minutes.

Patients will be randomised (3:1 ratio) to an intervention and a control group**.** The patients randomized to the intervention group will attend a total of 18 tailored exercise sessions (Three 40 minute sessions for six weeks) after their 6 weeks of chemoradiotherapy treatment. Where possible the exercise training sessions will be arranged to fit in with other appointments at the hospital. Patients randomized to the control group will be given best exercise advice and will be unsupervised. They will only attend an extra 3 sessions were a cardiopulmonary exercise test and VO2 Kinetics test will be performed. Patients will also be invited to attend 3 health related quality of life interviews at week 0, 3 and 6 during their exercise programme. These appointments will be directly before or after their exercise sessions to minimise hospital attendences.

Following surgery only routine clinically relevant observational data will be collected. These data will relate to hospital length of stay, the level of care required following surgery, post-operative morbidity survey (POMS) and the recovery process. Most of this information can be accessed from patient notes and on the electronic patient records system.

We aim to recruit 52 patients who will undergo long-course chemoradiotherapy and elective colorectal cancer surgery as an intention to treat. This sample size is calculated by using a 2 sample t-test, with 80% power to detect an estimated increase of 10% in VO2, based on the study of Kothman et al. Following Kothman et al we also estimated a drop-out rate of about 20%. **A subgroup of these patients (6 control and 6 exercise intervention patients) will be ask to consent separately for the muscle biopsies, the ^31^Phosphorus Magnetic Resonance Spectroscopy (^31^P MRS) scans and the blood samples.**

**HYPOTHESIS**

1. Interval exercise training will maintain or improve fitness (measured by anaerobic threshold) in patients undergoing neoadjuvant chemoradiotherapy.

2. Interval exercise training is safe and feasible in patients undergoing neoadjuvant chemoradiotherapy awaiting colorectal cancer resection.

3. Interval exercise training will improve other measures of physical fitness measured in the CPET and the oxygen uptake kinetics test.

4. Interval exercise training will improve quality of life in patients undergoing neoadjuvant chemoradiotherapy.

5. Improvements in physical fitness will reduce postoperative complications following major colorectal cancer surgery.

6. Does physical activity, measured by Sensewear Pro 3 activity monitors, decrease during neoadjuvant chemoradiotherapy and can this decrease be attenuated by an exercise training program?

7. Can we find an optimal time for surgery when fitness and cancer downstaging are at their best?

**HYPOTHESIS for Mechanism Pilot Study**

1. **To explore the exponential rate constant of post-exercise phosphocreatine recovery.**
2. **To explore the alteration in cellular and mitochondrial energetics eg. Change in mitochondrial numbers, change in mitochondrial activity and respiration.**

**Appointments**

**Cardiopulmonary Exercise Test (CPET)**

Six symptom limited Cardiopulmonary Exercise Tests (CPET) will be performed as part of the study occurring before and after the chemoradiotherapy treatment. Specifically, this involves cycling on an exercise bike for 8-12 minutes. Starting with a very low resistance on the pedals the patient will pedal at 60 revolutions per minute. After 3 minutes of cycling, the resistance will gradually increase at a constant rate until the patient can no longer turn the pedals at the required speed. The patient’s heart will be monitored by an electrocardiogram (ECG). The patient will wear a soft rubber mask in order to continuously sample expired air with an online breath by breath gas analyser. This test is common practice prior to operations and provides an accurate measure of physical capacity. A Near Infrared Spectroscopy (NIRS) probe will be attached to the thigh to non-invasively measure oxygen utilisation in the muscle by shining a light on to the thigh. Each CPET appointment will last approximately one hour. BORG scores will be assessed at intervals.

**Pulmonary Function Tests (PFT’s)**

The patients will perform pulmonary function tests (breathing tests). The breathing tests will be performed before and after the chemoradiotherapy treatment.

**VO2 kinetics test**

Patients will complete 2 submaximal / moderate exercise bouts on a cycle ergometer with 15 minutes rest between each bout. The test will consist of cycling at 10W for 3 minutes before the workload is abruptly increased to a workload equivalent to 80% of the estimated lactate threshold (estimated from the results of CPET) for a further 6 minutes. A NIRS probe will be attached to the thigh to non-invasively measure oxygen utilisation in the muscle (same as CPET). One of these tests will be done 72 hours after the first CPET test, whilst the other one will be incorporated into the exercise protocol (exercise session 17).

**Activity Monitoring**

Activity levels will be monitored by using a SenseWear Pro 3 activity monitor. Patients will wear an armband on the upper part of their dominant arm for a 3 day period. This will occur before, during chemoradiotherapy, during exercise training and 9 weeks post-exercise training. This will be done to assess changes in activity during the research process. These monitors will be fitted on routine care appointments.

**Muscle Biopsy**

**Muscle biopsies will be extracted using forceps, in each case approximately 20mg will be extracted. Muscle biopsies will be using an aseptic technique and local anaesthetic (1% lignocaine). Although there will be some stiffness following the biopsy (similar to a "dead leg"), this will disappear after 12- 14 days. These samples will take place prior to neoadjuvant chemoradiotherapy (NACRT), immediately after NACRT (at Week 0 prior to starting the exercise program), and on completion of the exercise programme (Week 6) as detailed in the flow-chart below.**

**Following extraction, muscle samples will be analysed for the following factors:**

- **Electron transport chain complexes**
- **Citrate synthase**
- **Mitochondrial function and respiration**

**These would give us an initial idea of whether mitochondria are being lost, or alternatively whether there is targeted complexes 1 and 3. We will also be looking for changes in:**

- **UCP3 uncoupling protein, thought to play a role in antioxidant defense or defense against lipotoxicity, but uncouples oxidative phosphorylation decreasing efficiency.**
- **PGC1alpha transcriptional regulator driving mitochondrial biogenesis**
- **PPARalpha fatty acid activated transcription factor drives expression of fatty acid oxidation enzymes (and UCP3)**
- **NRF1 nuclear respiratory factor 1, transcription factor driving expression of respiratory enzymes in mitochondria**
- **Mitofusin 2 drives mitochondrial fusion and is essential for maintaining mitochondrial morphology**
- **HIF1alpha transcription factor induced by hypoxia/oxidative stress.**

**Phosphorus magnetic resonance spectroscopy (^31^P MRS)**

**^31^P MRS studies of skeletal muscle bionergetics will be carried out on the 3T Siemens Trio scanner at the University of Liverpool Magnetic Resonance and Image Analysis Research Centre (MARIARC). This scan will take place prior to neoadjuvant chemoradiotherapy (NACRT), immediately after NACRT (at Week 0 prior to starting the exercise program), and on completion of the exercise programme (Week 6), as detailed in the flow-chart below.**

**Completion of an MR safety screening questionnaire will be performed on consent to the study to determine eligibility. On arrival at MARIARC the subjects will change into a hospital gown and proceed to the scanning room. The subject will lie flat on the scanner bed with the right leg semi-flexed over a custom-built exercise rig, with the ankle restrained by a velcro strap, and a ^31^P MR surface coil strapped to the anterior part of the thigh. A localising MR image will be acquired to assess coil placement. ^31^P MR scanning will be performed at rest, during and after short bouts of isometric knee-extension exercise at a rate of 0.5 Hz at various intensities: normally 2-5 min at each of 60% and 90% of maximum voluntary contraction, although this may be adjusted in preliminary pilot studies in this new patient group). Studies will take no more than 1 hour in the MR scanner.**

**^31^P MRS data will be analysed to quantify muscle cell pH, phosphocreatine (PCr) and inorganic phosphate (Pi), and kinetic analysis performed of the time-resolved data. The primary endpoint is the exponential rate constant of post-exercise PCr recovery, a measure of muscle mitochondrial function.**

**Standard MR exclusion criteria will apply (cardiac pacemaker, metal in eye, vascular clips, actual or possible pregnancy).**

**Study consent forms and MR screening forms will be kept in a locked filing cabinet. Names of subjects will be recorded, as is standard, in the MARIARC scanner logbook. Data from the studies will be kept securely on password-protected computers under coded identifiers only, without personal identifiers.**

**The main risks to the subjects are those related to MR. The use of a high magnetic field can cause injury (i.e. if the body contains any implanted magnetic material). Standard MR exclusion criteria will apply, and standard MR safety procedures will be strictly adhered to. All sequences are within NRPB guidelines for radiofrequency power deposition. MR scans are noisy, so subjects wear ear plugs. Safety is continually monitored both by the researchers and independently by responsible MARIARC personnel.**

**During scanning the subject will be continually monitored from the control room, and can abort at any time using a hand-held alarm. There will always be first aid- and resuscitation-trained personnel in the vicinity.**

**All relevant training and induction will be carried out. Guidelines and safety protocols have been made available to all investigators. The study will be managed, documented, monitored and reported according to standard MARIARC procedures. All aspects of the study will be monitored by the PI.**

**Blood tests**

**10mls of blood will be taken from each patient prior to neoadjuvant chemoradiotherapy (NACRT), immediately after NACRT (at Week 0 prior to starting the exercise program), and on completion of the exercise programme (Week 6). This will be processed as per Annex 1.**

**EXERCISE PROTOCOL – Intervention group**

Patients assigned to the intervention arm of the study will participate in a 6 week in-hospital, supervised exercise training program on a cycle ergometer. The training program will involve short periods of exercise at a high intensity interspersed with short periods of exercise at a moderate intensity. This mode of exercise training is termed aerobic interval training.

Exercise intensities during the interval exercise training program are specific to each patient and will be derived from the CPET test. Moderate intensity exercise is recognised as exercise below the anaerobic threshold. Patients will exercise at power outputs calculated to require 80% of the VO2 achieved at the anaerobic threshold (80%AT) for moderate intensity exercise. Heavy exercise is recognised as 50% of the difference between the VO2 at the anerobic threshold and the VO2 at peak oxygen consumption (50%∆). Patients will exercise at power outputs calculated to require 50%∆ for high intensity exercise.

Patients will attend 3 exercise sessions per week for 6 weeks. Each session will last <1 hour. Patients will be screened prior to each session to ensure that it is safe to perform exercise. Exercise training will involve repeated exercise bouts of 3 minutes at a moderate exercise intensity

(80%AT) followed by 2 minutes of exercise at a high intensity (50%∆) for a predetermined amount of time. In the first week of training, patients will perform the interval exercise protocol repeatedly

for 20 minutes (i.e. 4 repeated bouts of 3 minutes 80%AT and 2 minutes 50%∆). After the first week, the length of the training session will increase to 30 minutes for the remaining 5 weeks. 5 minutes of unloaded cycling will be performed at the start and end of the protocol for a warm-up and cool down. Blood pressure will be monitored every 3 minutes throughout exercise. Exercise sessions can be terminated by the patient at any time, and will be terminated by the supervisor of the test if any of the criteria to stop the test are met, based on the ATS CPET safety guidelines.

Patients will perform a CPET on the 1^st^, 7^th^ (session 1 of week 3) and 18^th^ exercise sessions (session 2 of week 6). Patients will be allowed 15 minutes to recover from the CPET and then asked to perform 10 minutes of the interval training (i.e. 2 repeated bouts of 3 minutes 80%VT and 2 minutes 50%∆). Exercise intensities for training will be adjusted based on the CPET data from the 7^th^ exercise session. Results from the CPET on the 18^th^ exercise session will be used to determine changes in exercise performance.

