**Control group**

Patients assigned to the control arm of the study will be given best exercise advice. These will be unsupervised and out of hospital. They will also have 3 CPET tests; at week 0, one in week 3 and one in week 6 to coincide with the CPET tests of the activity group. A VO2 Kinetics test will be done also on week 6, 72 hours after the CPET test.

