**Muscle Biopsy and 31 p MRS scan**

**Exercise Intervention Group**

(CPET at 0, 3 and 6 weeks)

Supervised – in hospital

QOL interview at 0, 3 and 6 weeks

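### The exercise arm's outcome CPET is tied to both a session number and a calendar week; the two labels conflict, and no rule says which governs when sessions are missed

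*Protocol*

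**What the plan says.** All references are to the protocol.

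- **EXERCISE PROTOCOL – Intervention group**, on the schedule: "Patients will attend 3 exercise sessions per week for 6 weeks". On the tests: "Patients will perform a CPET on the 1^st^, 7^th^ (session 1 of week 3) and 18^th^ exercise sessions (session 2 of week 6". On the outcome: "Results from the CPET on the 18^th^ exercise session will be used to determine changes in exercise performance".
- **Flow chart, exercise group:** "CPET at 0, 3 and 6 weeks". The control box carries the same line.
- **Control group:** "3 CPET tests; at week 0, one in week 3 and one in week 6". The stated intent is matched timing: "one in week 3 and one in week 6 to coincide with the CPET tests of the activity group". The controls' VO2 kinetics test follows in week 6, 72 hours after the CPET.
- **VO2 kinetics test:** one test is done 72 hours after the first CPET, "whilst the other one will be incorporated into the exercise protocol (exercise session 17". The tables under Exercise Intervention Protocol agree: session 17 is the kinetics test and session 18 carries a CPET.
- **Radiological Appointments:** all patients have further CPETs at 9 and 14 weeks after chemoradiotherapy.

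The protocol gives no visit window and no rule for what happens to a test when earlier sessions have been missed.

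**The concern.** The test that decides whether fitness changed should be due at the same time in both arms, whatever happens to treatment in between. Here the only sentence that names that test for the exercise arm identifies it by session number. Controls have no sessions and are tested by week.

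The two anchors agree only if every session takes place on schedule, which cannot be taken for granted. The protocol says "Patients will be screened prior to each session to ensure that it is safe to perform exercise", so some sessions may not go ahead. It makes safety and feasibility of training one of its hypotheses, and it allows for about 20% drop-out.

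If the session number is followed literally, a patient who stops training never reaches an 18th session. A patient who misses some reaches it late or not at all. No control can lose the test by that route. The patients affected would be those who attend least, so the week 6 comparison could set selected exercise patients against unselected controls, or compare patients at different times after chemoradiotherapy. Hypothesis 1 concerns anaerobic threshold, which is measured by CPET, so the main effect is involved.

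**Working it through.** **1. Do the session numbers and week labels agree?**

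Input: three sessions per week for six weeks, so 3 × 6 = 18 sessions. For session *s*, week = floor((*s* − 1)/3) + 1 and position in the week = ((*s* − 1) mod 3) + 1.

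| Session | Week | Position | Protocol's label | Agrees? |
|---|---|---|---|---|
| 7 | floor(6/3) + 1 = 3 | 0 + 1 = 1 | week 3, session 1 | yes |
| 17 | floor(16/3) + 1 = 6 | 1 + 1 = 2 | VO2 kinetics test, no week label | – |
| 18 | floor(17/3) + 1 = 6 | 2 + 1 = 3 | week 6, session 2 | **no** |

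The label on the 7th session reproduces; the label on the 18th does not. The second session of week 6 is the 17th, already assigned to the kinetics test.

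**2. Is the order of the week 6 tests the same in both arms?**

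- Exercise: kinetics test at session 17, then CPET at session 18.
- Control: CPET, then kinetics test 72 hours later.

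The order is reversed.

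**3. What does a missed session do under each reading?**

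- *Week governs.* The test falls in week 6 regardless. A missed training session other than the test visit has no effect on timing.
- *Session number governs, training ends at six weeks.* Anyone who has missed a session has no 18th session and therefore no test of the kind named.
- *Session number governs, missed sessions made up at three per week.* This rule is an illustration and is not in the protocol. With *m* missed, the 18th attended session falls in slot 18 + *m*: one missed gives week 7, session 1; three give week 7, session 3; six give week 8, session 3.

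**4. How many patients could be affected if the session number governs?**

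The protocol gives no attendance rate, so a range is assumed, with sessions independent and the same probability *p* of attending each. The exercise arm is 52 × 3/4 = 39.

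| Assumed *p* | P(all 18) = *p*^18 | Not all 18, of 39 | Mean weeks to 18 attended = 18/(3*p*) |
|---|---|---|---|
| 0.98 | 0.695 | 39 × 0.305 ≈ 12 | 6.12 |
| 0.95 | 0.397 | 39 × 0.603 ≈ 24 | 6.32 |
| 0.90 | 0.150 | 39 × 0.850 ≈ 33 | 6.67 |

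The third column counts everyone who misses at least one session, and matters only under the strict session-number reading with no catch-up within the six weeks. The last column applies only under the make-up illustration.

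**The case against.** A reader might infer that any missed session delays or removes the outcome test, and does so in the exercise arm only. The documents do not support that as a statement of fact:

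- The sentence that numbers the sessions also gives weeks for the 7th and 18th. The flow chart schedules both arms identically, and the control section says the tests are meant to coincide. Testing by week is an available reading and probably the intent.
- Nothing says that missed sessions are made up or that training runs beyond six weeks, so a systematic delay is not something the protocol prescribes.
- Permission to stop a session in progress is no evidence of missed sessions, because a session cut short has still been attended.
- Controls can also miss a week 6 visit, and the 20% drop-out allowance is not split by arm.
- The 9- and 14-week CPETs follow the calendar for everyone, so poor attenders do not vanish from all fitness comparisons.
- A reader might also conclude that the analysis becomes one of completers, or that the bias must favour training. The protocol states no analysis set, the SAP is not at hand, and the extent of natural recovery is not quantified.

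All of this stands and limits the point, but does not remove it. The week label on the outcome test is itself wrong, so it cannot settle which anchor governs. The sentence that names the test uses the session number. The later CPETs are not the ones named for change in performance. Stating that tests coincide does not help once an individual's sessions slip, because no control is paired with an exercise patient. And no analysis can recover a test that was never done.

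**Conclusion.** The point holds as a conflict and an ambiguity in the schedule of the outcome test. Two things are certain from the document: the 18th session cannot be the second of week 6 at three sessions per week, and the order of CPET and VO2 kinetics test in week 6 differs between arms.

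The possible bias is conditional. It arises only if the session number governs; then availability and timing of the outcome CPET depend on attendance in one arm. Its size cannot be derived. The figures of 70%, 40% and 15% attending all 18 sessions rest wholly on assumed rates of 98%, 95% and 90% and on independence between sessions. They show that full attendance should not be relied on; they do not predict how many tests would be lost. The direction of any bias is plausible but not established.

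**What to change.** Reconcile the sections EXERCISE PROTOCOL – Intervention group, Control group and VO2 kinetics test, the flow chart, and the session tables:

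1. Tie the week 6 outcome CPET and VO2 kinetics test to the same calendar week, counted from the same week 0, with the same window in both arms. Reconcile the order of the two tests.
2. State that both tests are due whatever number of sessions has been attended, including for patients who have stopped training, subject to the protocol's own safety screening.
3. Name the outcome test as the Week 6 CPET in place of the session number, and correct the session and week label.
4. Record sessions attended separately, as adherence.

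The 7th-session CPET also serves to adjust training intensity. How that use fits with missed sessions is for the sponsor to reconcile.

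The cost is protocol wording; no test is added. The one downside is that poor attenders would be tested after fewer sessions, so the estimated effect may be slightly smaller.

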**Control group**

Patients assigned to the control arm of the study will be given best exercise advice. These will be unsupervised and out of hospital. They will also have 3 CPET tests; at week 0, one in week 3 and one in week 6 to coincide with the CPET tests of the activity group. A VO2 Kinetics test will be done also on week 6, 72 hours after the CPET test.

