**VO2 kinetics test – Session 17**

**Interval exercise training sessions 7 and 18**

| **CPET and 10 minutes exercise** | | | | | |
| --- | --- | --- | --- | --- | --- |
| **CPET** | **15 minutes recovery** | **3 mins 80%VT** | **2 mins 50%∆** | **3 mins 80%VT** | **2 mins 50%∆** |

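### The week 6 VO2 kinetics test precedes the CPET in the exercise arm but follows it by 72 hours in controls, and the CPET that sets its work rate is not named, so the between-arm comparison may be confounded

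*Protocol*

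**What the plan says.** **Exercise arm.** The section on the VO2 kinetics test describes two tests. The first comes 72 hours after the first CPET, "whilst the other one will be incorporated into the exercise protocol (exercise session 17"). The session tables agree: "VO2 kinetics test – Session 17". The exercise protocol for the intervention group places CPETs at the 1st, "7^th^ (session 1 of week 3) and 18^th^ exercise sessions (session 2 of week 6"), and the tables also put a CPET in session 18.

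**Control arm.** CPETs take place "at week 0, one in week 3 and one in week 6 to coincide with the CPET tests of the activity group". The section then adds: "A VO2 Kinetics test will be done also on week 6, 72 hours after the CPET test".

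**Work rate.** The step is set at "80% of the estimated lactate threshold (estimated from the results of CPET"). Nothing says which CPET this means at week 6, in either arm. The session 7 CPET is given one use only, which is to adjust training intensities.

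**Control visits.** The Overview says of controls: "They will only attend an extra 3 sessions were a cardiopulmonary exercise test and VO2 Kinetics test will be performed".

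**Role of the test.** Hypothesis 3 names the oxygen uptake kinetics test, alongside other CPET measures, as a place where training should show benefit. Hypothesis 1 concerns the anaerobic threshold.

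**The concern.** An outcome compared between randomised arms should be measured in the same way in both. Here the schedule itself differs by arm.

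- **Information available.** The load depends on a threshold taken from a CPET. The position of the test relative to the week 6 CPET decides whether a current threshold exists when the load is set.
- **Comparability with baseline.** The first kinetics test follows a CPET by 72 hours, with no distinction by arm. At week 6 controls repeat that sequence and exercise patients do not, so change from baseline is also measured under different conditions.
- **Calendar position.** The control CPET is meant to coincide with session 18. The control kinetics test therefore falls about 72 hours after the point that matches session 18, whereas the exercise test falls before it.

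At stake is whether a difference in kinetics, or in the near-infrared muscle signal recorded with it, can be credited to training. Part of it could come from how the test was set up.

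**Working it through.** **1. Session numbering.** The input is "Patients will attend 3 exercise sessions per week for 6 weeks", so 3 × 6 = 18 sessions. For session s, week = floor((s − 1)/3) + 1 and place in week = ((s − 1) mod 3) + 1.

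| Session | Week | Place in week | Content |
|---|---|---|---|
| 7 | 3 | 1st | CPET |
| 17 | 6 | 2nd | VO2 kinetics test |
| 18 | 6 | 3rd | CPET |

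The Protocol's label for session 7 is reproduced. Its label for session 18 as the second session of week 6 is not: by this count it is the third. By session number, which the text and the tables share, 17 still precedes 18.

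**2. Order and available CPET at week 6.**

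| | Exercise arm | Control arm |
|---|---|---|
| Order | Kinetics test, then CPET | CPET, then kinetics test |
| Gap between the two | Not stated | 72 hours |
| Latest CPET available to set the load | Session 7 (week 3) | Week 6 |
| Repeats the baseline sequence | No | Yes |

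**3. Possible intensity mismatch (illustration).** Let c be the proportional change in a patient's threshold since the CPET that set the load, on the scale on which the load is set. The test is then run at 80/(1 + c) per cent of the current threshold. The Protocol gives no value for c between weeks 3 and 6, so a range is shown. It applies to the exercise arm only if the session 7 CPET is the source.

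| Assumed c | Calculation | % of current threshold |
|---|---|---|
| −10% | 80/0.90 | 88.9 |
| 0 | 80/1.00 | 80.0 |
| +5% | 80/1.05 | 76.2 |
| +10% | 80/1.10 | 72.7 |
| +20% | 80/1.20 | 66.7 |

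Controls would be at 80% if their week 6 CPET is the source. The gap would be 80 − 76.2 = 3.8 points at +5% and 80 − 72.7 = 7.3 points at +10%.

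**4. Does a common week 3 source remove the mismatch?** Suppose exercise patients gain 10% after week 3 and controls do not change (both assumed). With the week 3 CPET in both arms, exercise patients are at 80/1.10 = 72.7% and controls at 80/1.00 = 80%. The 7.3-point gap remains. Order and source are then equal, but relative intensity is not.

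**5. Control visits.** CPETs at weeks 0, 3 and 6 make three visits. A kinetics test 72 hours after the last one makes 3 + 1 = 4, against three in the Overview.

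**The case against.** The strongest reply is that the Protocol never says the two arms use different CPETs. A reader might infer that controls are tested at their week 6 threshold and exercise patients at their week 3 threshold, but that holds only if the most recent CPET is always used. One earlier CPET could set the load in both arms, and the source would then not differ. This stands: different sources are possible, not established.

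A reader might also infer that the comparison is biased, with exercise patients tested too lightly. The text does not support that either. Direction and size depend on an unknown change in threshold, and the mismatch vanishes if there is none. The only effect size in the Protocol, a 10% increase in VO2, is not tied to weeks 3 to 6. Even 76.2% and 72.7% stay below the threshold, within what the Protocol calls moderate exercise, and no effect on a kinetics parameter is given. This stands too.

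The contrast in what precedes the test is also limited. The interval between sessions 16 and 17 is not stated, and no carry-over at 72 hours is shown.

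The reversed order survives all of this. It is written into the schedule and differs by arm whichever CPET sets the load. An unnamed source would matter little under a common schedule. Here it matters because the schedule gives one arm an option that the other lacks.

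**Conclusion.** The week 6 kinetics test is scheduled in opposite order to the CPET in the two arms, and its source CPET is not named. The work rate may therefore rest on different CPETs, only controls reproduce the baseline sequence, and the between-arm comparison of oxygen uptake kinetics may be confounded. The order difference comes straight from the text and needs no assumption. The size of any intensity mismatch cannot be derived from the Protocol; the percentages above are illustrations under assumed threshold changes.

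The consequences are confined to the kinetics part of hypothesis 3. Hypothesis 1 rests on CPETs that are timed to coincide between arms, and the sample size is based on VO2, so neither is affected. The point deserves correction but does not endanger the main aim of the trial.

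The control visit count is a separate, minor contradiction that holds without any assumption.

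**What to change.** Reconcile the Overview, the VO2 kinetics test section, the exercise protocol for the intervention group, the Control group section and the session tables, so that both arms share:

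1. the same order of CPET and kinetics test at week 6;
2. the same gap between them;
3. the same named CPET as the source of the work rate.

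The preferred version puts the week 6 CPET before the kinetics test in both arms, for example by exchanging the tests at sessions 17 and 18, and sets the work rate from that CPET. This equalises relative intensity and matches the baseline sequence. Using the week 3 CPET with the kinetics test first in both arms is a weaker alternative: it equalises order and source, but leaves relative intensity unequal if thresholds diverge after week 3.

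In the same edit, state the second kinetics test for controls in the VO2 kinetics test section, which at present describes it only as session 17. Correct the place of session 18 within week 6, and bring the control visit count in the Overview into line with the final schedule.

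The cost is wording and minor rescheduling to fit the gap into week 6. No test is added, and controls already need a separate visit for the 72-hour gap. Tests already done under the unequal schedule cannot be repeated, so the change is best made before patients reach week 6.
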